### Recruitment and randomisation

We will recruit students and teachers at the school level using 1.) Personal introductions to schools via our research partner, Educator School Centres Ireland’s (ESCI), who host continuing professional development (CPD) for teachers/schools on behalf of the Department of Education and Skills, 2.) Body Confident Schools webinar event for schools (a single online event for schools, hosted by ESCI & Jigsaw, The National Centre for Youth Mental Health), 3.) Advertisement on social media & website pages, 4.) Cold call invitations.

Schools will be selected on the basis of 1.) their expressed interest and 2.) their fit with recruitment criteria. Prior to randomisation, schools will be stratified based on school categorisation (e.g., urban/rural and single sex/coeducational) to ensure the gender and geographical location of participants in each treatment group is closely balanced. A stratified shortlist of 26 schools will be allocated using covariate-constrained randomisation, a type of minimisation randomisation, with the R statistical package cvcrand (https://cran.r-project.org/web/packages/cvcrand/cvcrand.pdf). Allocation will be constrained by a.) the number of boys and b.) the number of girls in TY in each school, and c.) the school’s location categorisation (urban/rural). Shortlisted schools registering interest that decline to participate after initial contact will be replaced by schools on the waitlist based on minimisation, or replacement by same category method. Given the nature of the study, blinding participants to their condition will not be possible.

### Procedure

Informed active consent will be sought from school principals (during recruitment) and we will also seek informed consent from teachers (before teacher training), parents (before baseline assessment) and assent from students (at baseline assessments). On receiving principal consent to participate, the researcher will liaise with a nominated staff member to coordinate involvement. Optional virtual ‘zoom check in’ meetings with the primary researcher will be offered to parents and students prior to participation in addition to teachers throughout the trial to address queries/issues about the programme/research. Students without consent to participate will be given the option to attend supervised study period or another school-based activity during time allotted to the intervention. Participants can withdraw from participation at any point without explanation.

Data will be collected via participant self-report to standardized questionnaires delivered in an online format using an online platform (e.g., SurveyMonkey) or in pen and paper format (as per the preferences of the school). Questionnaires will be administered to students by a member of the research team under exam-like conditions. In the post-intervention questionnaire, students in the experimental group will be asked additional questions about their perceptions of the programme. Teachers in the experimental group will also complete fidelity checklists after each lesson and a short questionnaire on completion about perceptions of the programme. On study completion, participants will receive a full debrief and contact details for relevant support services. Schools will receive a €200 financial honorarium for participating.

#### Teacher training

Teachers in the intervention group will attend a comprehensive 2.5 hour in person/online training session, delivered by the primary researcher (curriculum writer on the BodyKind programme and body image researcher) prior to programme delivery (August/September 2023). Teachers will be provided instruction on how to deliver the programme content and materials and encouraged to implement the programme as close to the teacher manual as possible over a four-week period. Teachers will receive a teacher training manual and access to over 2.5 hours of self-guided videos and online resources linked with the Be Real foundation to support delivery. Teachers in the waitlist condition will receive teacher training after data collection is completed.

### Measures

#### Student questionnaire

We will consult with student members of the Irish Second-Level Students Union of Ireland (ISSU), the national umbrella body for second-level students in Ireland, on the comprehension and suitability of the questionnaire schedule prior to administration to students. Two attention check items will be placed throughout the questionnaire to screen out participants who are not focused or paying attention (e.g., show you are paying attention by disagreeing below). Items will be randomized within scales to avoid order bias.

##### Demographic characteristics

Participants will report on age, gender and ethnicity. Single items assessed gender/sexual orientation, ethnicity/race, perceived body size, frequency of negative appearance commentary from peers based on appearance, and frequency of appearance-related social media use (i.e., hours spent using Instagram, TikTok, Snapchat or YouTube per day).

##### Primary outcomes

Body Appreciation Scale-2 (BAS-2; [58] is a 10-item scale. Responses to items such “I feel good in my body” are indicated on a 5-point Likert Scale (1-5), with higher scores indicating higher levels of body appreciation. BAS-2 demonstrates good validity and reliability among international adolescent samples [59].

Body Satisfaction Visual Analogue Scales (VAS; [60]) Items from the appearance/weight subscales of the Eating Disorder Examination Questionnaire will be adapted (EDEQ; [61]) as 100-point visual analogue scales (VAS) to assess state body satisfaction with various aspects of appearance. As per Durkin & Paxton [60] participants will use a 100-point slider 0 (not at all satisfied) and 100 (very satisfied) to rate how satisfied they feel with their body shape, weight, and size. Participants will also rate their satisfaction with height, muscle mass/tone and overall appearance. A mean score from the six appearance dimensions will be calculated, with higher scores representing higher state body satisfaction. This approach has been shown to have good convergent validity with the Eating Disorder Inventory Body Dissatisfaction Subscale in adolescents (*r* = -62; [60]).

The Five-Item World Health Organisation Wellbeing Index (WHO-5; [62]) is a unidimensional scale that measures emotional wellbeing using five positively worded items. Participants indicate the extent to which positive feelings, such as “I have felt calm and relaxed” were experienced over the last two weeks, using 6-point Likert scales ranging from 0 (not present) to 5 (constantly present). Raw scores are transformed to a score from 0 (worst thinkable well-being) to 100 (best thinkable well-being) with scores <50 suggesting poor emotional well-being [63]. The WHO-5 has been validated for use with adolescents and has adequate validity as an outcome measure in clinical trials [62, 63].

##### Secondary outcomes

The Self-Compassion Scale for Youth (SCS-Y;[64]) is a shortened and modified version of the Self-Compassion Scale (SCS; [65]) developed for use with adolescent populations. The SCS-Y is a 14-item scale that contains subscales for the aspects of compassion as identified by Neff [65]; self-kindness, self-judgement, common humanity, isolation, mindfulness and over identification. Participants respond to items such as “When I feel frustrated or disappointed, I think about it over and over again.” on 5-point Likert scales ranging from 1 (never) to 5 (always). Negatively worded items are reverse coded. Higher scores indicate higher levels of self-compassion. The SCS-Y has been validated among adolescents aged 12-17 years, where mean scores range between 1.0-2.49 (low), 2.5-3.5 (moderate), and 3.51-5.0 (high) and demonstrated good levels of internal consistency with Cronbach's alpha of >=.82 for each subscale.

Internalization-General subscale of the Sociocultural Attitudes Towards Appearance Scale-3 (SATAQ-3; [66]), will be used to assess internalization of social media ideals. Items were adapted to social media by substituting the words “social media” into item stems e.g. “I would like my body to look like people on social media”. The five-item scale is measured using five-point Likert scales ranging from 1 (definitely disagree) and 5 (definitely agree). Negatively worded items are reversed coded and items are averaged to yield a mean score, with higher scores indicating greater body ideal internalization. The original scale has been shown to be a reliable in adolescent girls and boys [67] and the adapted scale has been found demonstrate good psychometric properties and good levels of internal consistency, ranging from α = 0.75 among male, and α = 0.84 among female adolescents [43, 68].

The Appearance-Related Social Media Consciousness Scale (ASMC, [69]) is a 13-item scale that captures the extent to which individuals’ thoughts and behaviours reflect ongoing awareness of whether they might look attractive to a social media audience. Given that appearance-related use is a more important predictor of body dissatisfaction compared with general/non-visual social media use [70], this measure is important to include. Items such as “I think about how specific parts of my body will look when people see my pictures on social media” are measured using 7-point Likert scales ranging from 1 (Never) to 7 (Always). ASMC scores demonstrate strong internal consistency, convergent and incremental validity, and test-retest reliability in adolescent boys and girls [69].

Body Appreciation for Others Subscale of the Positive Body Image in Adolescents Scale (PBIAS; [71]) measures young people’s capacity to appreciate and respect other people’s diverse bodies and appearance, which is another element of positive body image. Participants respond on 7-point Likert scales ranging from 1 (strongly disagree) to 7 (strongly agree) to items such as “It is my hope that everyone is able to love their bodies as they are”. The body-other appreciation subscale shows good validity and, with McDonald’s (1999) coefficient omegas of ωh=.88 indicating good reliability.

The Compassion Towards Others Action Subscale of the Compassionate Engagement and Action Scales Youth (CEAS-Y, [72]), measures compassion in adolescents. The 4-item action orientation competency subscale focuses specifically on actions aimed to prevent and alleviate distress/suffering in others, such as “When others are distressed or upset by things, I am kind and supportive to them”. Participants respond using 10-point Likert scale from 0 (never) to 10 (always) with higher scores indicating higher compassionate action orientations towards others. This subscale shows good internal consistency with alpha values across items ranging between α=.84-.88 in adolescent boys and girls [72].

Appearance related social advocacy [46] is a purpose-built scale measuring appearance-related social justice/advocacy motivations/intentions which align with key aims of the BodyKind programme. Participants indicate on 5-point Likert Scales whether they 1 (disagree) or 5 (agree) with the three items asking if 1.) they are aware of experiences of people who look different to them, 2.) know how to promote fairness/equality for individuals regardless of appearance and 3.) have intentions to take action to challenge appearance bias. The three items are summed to give a total score, with higher scores indicating higher motivations/intentions for appearance-based social advocacy. This scale has demonstrated reasonable reliability in pilot studies with adolescents in the USA (α=.75) [46].

#### Student feedback questionnaire

After receiving the BodyKind programme, students in the intervention group will complete additional questions assessing perceptions of programme acceptability and perceived attainment of learning objectives. Open-ended questions will capture ways students have applied content to their personal lives, key programme take home messages and suggestions for programme improvement. See Additional file 1: Appendix A.

#### Teacher fidelity checklists

Teachers will complete a checklist at the end of each lesson indicating the extent to which they covered key aspects of the lessons. See Additional file 1: Appendix B.

#### Teacher questionnaire

After delivering the BodyKind programme, teachers will complete a questionnaire on their perceptions of their own delivery, student engagement, and perceived suitability of the programme for students and teacher’s attitudes towards the programme. Teachers will also be asked about their perceptions of the teacher training and teacher resources (manual/worksheets). Open ended questions will capture liked/disliked aspects of the programmes, teacher modifications to the programme and teacher suggestions for improving the programme to inform optimisation of programme implementation going forward. See Additional file 1: Appendix C.

### Implementation quality evaluation

Four dimensions of implementation quality will be assessed; 1. dosage (number of sessions delivered/attended), 2. fidelity (extent to which programme is delivered as intended), 3., quality (how well the programme is delivered by the facilitator), and 4., responsiveness (how well participants engage with the programme). As per Dowling & Barry [52], dimension scores will be combined to yield a total implementation quality index score which indicated schools as either high- or low- implementors. Dimensions will not be weighted as each dimension is considered equally important in this implementation quality index. Qualitative data will be used to expand on potential factors influencing programme implementation.

#### Dosage

Will be assessed via two indicators. 1.) Teachers will indicate if they delivered the lesson (Yes=1, No=0) and this will be summed across all four lessons, 2.) Students will indicate on the Student Feedback Questionnaire (Yes=1, No=0) if they remembered attending each of the four lessons, this will be summed across all lessons and student scores will be averaged for each school.

#### Fidelity

Although observational methods (i.e., audio recordings) are considered gold standard for assessing fidelity, they are time and resource intensive and may change behaviours of those being observed. Self-report checklists are widely used as practical and acceptable measures to assess fidelity [73, 74].

Fidelity, will be measured via two indicators. 1.) Teachers will indicate (1=yes, 0=no) whether they covered the key items/concepts on fidelity checklists for each lesson. There are 7 items on the checklist for each lesson, which will be summed across all lessons. 2.) In post-intervention questionnaires, teachers will be asked to indicate the degree to which they implemented the programme as instructed in the teacher training manual using visual analogue scales ranging from (0=Not at all, 100 = Very Much So).

#### Quality of delivery

Will be assessed using two indicators. 1. ) Students will indicate the extent to which they agree with the statement that the “Lessons were taught well by the teacher” using VAS scales ranging (0 = Disagree , 100 = Agree). 2.) Teachers will rate the extent to which they felt confident delivering the programme using VAS scales ranging (0=Disagree , 100=agree).

#### Responsiveness

Will be assessed using four indicators. 1.) Students’ responses to 6 items, indicating the extent to which they understood, paid attention, enjoyed, felt comfortable participating in the programme and believed the programme was relevant and important using VAS scales ranging from (0=Disagree , 100=agree). A mean score for each of the six items will be calculated for each student, and then, a mean score will be calculated by averaging the student scores within each school. 2.) Students’ overall rating of the programme from 0=very poor to 10=excellent.

3.) Teacher perceptions of student responsiveness will be assessed via 5 items, where teachers indicate the extent to which they believe students understood, engaged with and enjoyed the programme and the extent to which students gave their best effort in assessments using VAS scales ranging (0=Disagree , 100=Agree). A mean score for each of the five items will be calculated for each teacher. 4. Teachers also indicated their likelihood to recommend, implement the programme in the future (0=Disagree , 100=Agree) and their own satisfaction with the programme (0=Completely Dissatisfied, 100 = Completely Satisfied).

### Intervention

#### Programme development

BodyKind was developed in partnership with the Be Real USA, NFP (https://berealusa.org/) and an international team of body image researchers and health curricula writers. BodyKind content was based on the literature and existing programmes including The Body Project [19, 75] and Dove Confident Me [76], as well as pilot work from the self-compassion intervention Digital SMART [32]. BodyKind was refined through iterative trials with Be Real research interns as well as acceptability trials with students and health teachers in high schools across the USA [46].

#### Theoretical basis

BodyKind is designed to target risk factors for body dissatisfaction and strengthen positive body image using a multipronged approach. The programme incorporates cognitive dissonance, where students are encouraged to think critically about the costs (time, money, energy) of pursuing appearance ideals, with the view to reducing internalisation of and comparisons with body ideals [45, 75]. This programme also extends critical thinking to challenge unhelpful diet culture myths that underpin appearance concerns [77, 78]. Through a Myth Busting Activity, students learn to challenge the notion that “we can all achieve body ideals with sufficient hard work and effort” by learning about the biological limits of body change and how factors outside of our control, including genetics, influence shape/size, not only willpower and self-control [79]. Students also learn to challenge the ideas that “highlighting someone’s body ‘flaws’ will motivate them to engage in health behaviours” through learning about the counterproductive effects of body shaming for health [80]. Students also are encouraged to identify the issues with conflating health and appearance (i.e., recognising that appearance is often a poor indicator of physical/psychological health). It is anticipated that by challenging diet culture myths, there will an increased sense of awareness and understanding around complex factors that influence our bodies and body image and reductions in body-related self-blame and shame [29].

Students are also introduced to the concept of self-compassion which involves 1.) kindness, which involves non-judgement, self-care and empathy towards oneself, 2.) mindfulness, the capacity to view situations from a balanced perspective and 3.) common humanity, the ability to recognise that all humans are imperfect and experience similar difficulties in life [81]. Students reflect on how appearance pressures may show up in their own lives and on social media and learn, through experiential exercises, how to reframe unhelpful critical thoughts into kinder, soothing, self-compassionate ones in order to reduce body dissatisfaction. Learning to appreciate alternative aspects of themselves rather than overvaluing appearance and recognising that no-one is perfect (i.e., common humanity), is thought to improve functional and aesthetic body appreciation [27, 82].

This programme uniquely seeks to foster ‘compassion for others’ as a way of building positive body image [38]. Students learn about Appearance Bias -when a person is judged and treated differently based on how they look, rather than who they are or how they behave. Negative bias can lead to discrimination, and positive bias can manifest as "pretty privilege" where a person is treated better because they look like society's appearance ideals. Students read a collection of other people's body stories, gaining an awareness of how people of different sizes and abilities, with different skin shades, facial features, sexualities and gender representations experience the world. Students are also encouraged to think about ways they reduce appearance pressures and build a kinder environment for themselves and others, for example through reducing 'body talk' that reinforces unhelpful societal beliefs about appearance [37, 40].

Students explore how viewing their bodies as instruments, not ornaments; gratitude; and the acceptance of natural body diversity can lead to body confidence [83–85]. Students also hear about people's journeys from more negative to more positive body image, which is designed to help students model paths to more positive body image [86].

Incorporating social justice perspectives [35], students are given the tools to become agents for change and focus on real steps they can take to create a better world. Students receive guidance on creating their own Roadmap to Action which takes an idea from the issue stage to an action stage. They will learn tangible steps to create an action plan to address a body image issue they feel strongly about in this programme, empowering them to make positive changes in their communities and beyond which has been identified as a way to build positive body image in adolescents [84].

#### Structure & content

Each 50-minute lesson introduces a different theme/topic related to body image and incorporates a range of learning strategies to build skills in self-compassion, critical thinking, emotional regulation, social activism which are designed to support positive body image and psychological wellbeing. Table 1 outlines content and structure of the BodyKind programme.

**Table 1 Tab1:** BodyKind lesson content overview

**Lesson**	**Learning objectives**	**Learning strategies**
1. Challenging appearance bias	• Understand Appearance Bias and the many ways people experience Appearance Pressure • Empathise with a diverse range of people and their experiences of their bodies & see own experience reflected in the stories • Learn how to incorporate Body Confidence tips into their lives (i.e., body functionality, gratitude, appreciation)	• Framing the topic of Appearance Bias • Body stories gallery walk to learn about other people’s experiences of body image. • Written reflection on ways to boost body confidence
2. Self-compassion and social media	• Students understand the impact of comparisons (on social media and elsewhere) • Students learn to recognize their own Inner Critic • Students learn to use Self-Compassion to be less harsh to themselves	• Self-compassion jigsaw activity to understand key components of self-compassion • Written reflection on self-compassionate social media use
3. Compassion for others	• Students challenge unhelpful cultural messages about appearance • Students recognize the impact of Body Talk with emphasis on the reaction of the person who is the subject of Body Talk • Students can identify ways to model other people’s journeys from negative to more positive body image.	• Myth busting activity on cultural messages • Discussion on teasing and compliments • Video of teenagers describing how they moved from a more negative to a more positive conceptualisation of their bodies • Letter to a friend activity where students apply concepts of self-compassion, body functionality, gratitude, body diversity, and Body Talk in addition to lessons in the stories of people who are now more body confident.
4. Taking action	• Determine an appearance-related topic they are interested in taking action on (e.g., challenging appearance bias) • Create a plan for positive change • Reflect on what they have learned in this process and this program	• Roadmap for taking an idea from issue to action guided activity • Bingo to revise key concepts.

## Data analysis

### Effectiveness trial

#### Data screening

Cases with more than 70% missing data, inappropriate responses, missed attention checks or no baseline data or surveys completed under 3 minutes or that cannot be matched with another time point, will be removed. This study will primarily report outcomes of Intention to Treat analyses, where all participants randomised to a condition are included in the linear mixed model. A per protocol analysis that comprises of those who provide outcome data and pass attention control checks will be reported as a secondary analysis.

Data will be screened for missing data. If the missing data is substantial (> 5%), a sensitivity analysis will be conducted. Multiple Imputation (MI) will be conducted using the Multiple Imputation Analysis function on SPSS. Under MI in SPSS, the Fully conditional specification (MCMC) method will be chosen. As recommended by Heymans and Eekhout [87], we will specify 50 iterations using Predictive Mean Matching (PMM) for continuous variables.

Prior to conducting inferential statistics, data will be screened for missingness, outliers, normality and model assumptions. Data will be summarised graphically and by using descriptive statistics.

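### Data screening removes randomised students partly on follow-up data, yet the next sentence calls the primary analysis Intention to Treat with everyone randomised included

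*Protocol article*

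**What the plan says.** Three consecutive statements under Data screening define the analysis sets.

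- Removal applies to "Cases with more than 70% missing data, inappropriate responses, missed attention checks or no baseline data or surveys completed under 3 minutes". The same sentence ends with a further ground, the matching rule: "or that cannot be matched with another time point, will be removed". No wave is named for the missingness, attention-check or duration rules.
- Primary analysis: "Intention to Treat analyses, where all participants randomised to a condition are included in the linear mixed model".
- Secondary analysis: "A per protocol analysis that comprises of those who provide outcome data and pass attention control checks".

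The same section plans multiple imputation as a sensitivity analysis when more than 5% of data are missing. It does not say that removed cases return for it.

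Two other places bear on the rules. The Student questionnaire section states: "Two attention check items will be placed throughout the questionnaire to screen out participants who are not focused or paying attention", again without a wave. The Procedure section states: "In the post-intervention questionnaire, students in the experimental group will be asked additional questions about their perceptions of the programme".

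**The concern.** An Intention to Treat analysis keeps the groups as randomised. Here the set is first filtered on information that can arise after allocation, and the result is then given the Intention to Treat label. The clearest case is the matching rule: whether a second time point exists is itself a follow-up outcome.

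The mixed model and the imputation are the plan's tools for students with incomplete follow-up, but the screening step removes those students first. An analyst could follow either sentence, obtain two different primary populations, and report either as planned. The secondary analysis offers little contrast, because it applies much of the same filter again.

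**Working it through.** The plan attaches no figure to this point, so the check sets the three statements side by side. T1, T2 and T3 are baseline, post-intervention and 2-month follow-up.

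| Student's data | Removal rule | Intention to Treat sentence | Per protocol sentence |
|---|---|---|---|
| T1 only | removed, no second time point | in | out, no outcome data |
| T1 and T3, no T2 | kept | in | out, if outcome data means T2 |
| T1 and T2, attention check missed at T2 | removed | in | out |
| T1 and T2, T2 survey under 3 minutes | removed | in | not restated; already gone if drawn from screened data |
| T1 and T2, no quality flag | kept | in | in |

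**Removal against Intention to Treat.** The second and third columns disagree in rows 1, 3 and 4. Row 1 does so whichever wave the quality rules were meant for.

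**What the matching rule sorts on.** The primary comparison under Data analyses uses T1 and T2. For that comparison, rows 1 and 2 carry the same information, a baseline score and no T2 score. One student is removed and the other kept, purely on response at T3.

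**Imputation.** If screening comes first, as the order of the text suggests, T1-only students are gone before missingness is compared with the 5% threshold. The people most in need of imputation then neither trigger it nor enter it.

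**Screened set against per protocol.** Within the screened data, the two sets differ mainly in row 2. Lessons delivered and attended (Dosage) and checklist coverage (Fidelity) are collected, but neither enters the per protocol definition.

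**Three-minute rule by arm.** Let c be the time spent on the common items and e the time spent on the extra programme questions. In control, a T2 survey is flagged if c < 3. In the intervention arm, if all items are timed together, it is flagged if c + e < 3, that is c < 3 − e. With e > 0 the limit is easier to pass in the intervention arm. If the extra items are timed separately, e drops out and the rule is equal. The article gives neither e nor the timing method.

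**Size of bias.** The estimand is the Time*Condition interaction, a difference in change. Let a share p of students be removed in each arm, and let g be the difference in mean T1-to-T2 change between removed and retained students. The retained mean change equals the full mean change minus p × g, so

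bias = p(control) × g(control) − p(intervention) × g(intervention).

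If removed students differ only by a constant level s at both waves, then g = s − s = 0 and the bias is zero for any p. The document supplies neither p nor g.

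**Margin.** The article asks for 504 students and recruits 600: 600 − 504 = 96, and 96/600 = 16%. Screening removals draw on the same 16% as attrition. The 504 is taken as printed. From d = .2, power .80 and two-sided alpha .05 alone, an independent comparison needs 393 per arm, 786 in total. The repeated-measures calculation also needs a within-person correlation that is not printed, so 504 can be neither confirmed nor refuted.

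**The case against.** The strongest reply is that a journal article condenses a longer protocol, which may say at which wave each rule applies, what a case is and how time is recorded. That is fair for those details, and nothing here rests on their absence. It does not answer the contradiction, because both rules are stated and they conflict.

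The matching rule might also refer to linking records by identifier. Unlinkable follow-up records are a real problem, but the wording does not separate them from a baseline survey with no later response, and the latter is caught as written.

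Four stronger readings are tempting, and the document does not support them.

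- *The 3-minute rule is arm-dependent.* It is worded identically for both arms. Unequal action is an inference that holds only if the extra questions are timed with the rest. The article elsewhere treats them as a named student feedback questionnaire, and surveys are given under exam-like conditions, which may limit speeding. Nor does anything say that these items count towards the 70% missingness base.
- *Survey mode biases the comparison.* Paper or online is a school preference in both arms, and no arm difference is documented.
- *The bias is 10% to 25% of the target effect.* A reader might multiply a 4- or 10-point difference in removal by .5 SD (.04 × .5 = .02; .10 × .5 = .05, against d = .2). That uses a difference in level, which cancels from the change contrast when whole cases are removed, and none of those inputs comes from the document.
- *The per protocol analysis cannot differ at all.* It can, through students with T1 and T3 but no T2.

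One caution about remedies also stands. Student attendance is recalled on a questionnaire that only intervention students complete. A per protocol set built on it would filter one arm on post-randomisation data and leave the other untouched.

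**Conclusion.** The point holds as a contradiction in the definition of the primary analysis population. Followed literally, the removal rule deletes randomised students partly on follow-up response and produces a selected set that would be reported as Intention to Treat. This rests on the wording alone, and the T1-only case establishes it without any assumption about waves or timing.

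The per protocol set nearly duplicates the screened set and carries no adherence criterion, so its name misdescribes it. Unequal action of the 3-minute limit is a possibility, conditional on joint timing. No bias has been demonstrated: its size and direction depend on how many students are removed in each arm and how their change differs, and the article gives neither. The only size available is the planned margin of 96 students (16% of 600), which screening removals share with attrition.

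**What to change.** 1. Define the primary set as every eligible, consented student with baseline data, analysed in the arm of the school. Keep baseline-only students through the mixed-model likelihood or through imputation. Describe the set in those words, since students without baseline data are still outside it.
2. Drop the matching rule for students who simply lack follow-up. If it is needed for records that cannot be linked by identifier, say so separately.
3. In the primary analysis, limit response-quality exclusions to the baseline survey at most, and report them by arm. The article does not say that baseline precedes school allocation, so even these are not automatically neutral.
4. Move T2 and T3 exclusions for attention checks, completion time and missingness above 70% to a sensitivity analysis, with time and missingness counted only on items common to both arms.
5. Rename the per protocol set as a response-quality or completer sensitivity analysis. Do not redefine it by attendance recalled in the intervention arm only.

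The cost is wording in the analysis section, with no change to data collection. The downside is small: some noisy follow-up responses stay in the primary analysis, and the sensitivity analysis shows whether they matter.
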